**Table 6-8 Dose Modifications for Non-hematologic Toxicity**

| Recommended Action                                                                                        |                                                                                                                                                                                                                                                                                       |                                                                                                                                                                                                                                                                                       |
|------------------------------------------------------------------------------------------------------------------|---------------------------------------------------------------------------------------------------------------------------------------------------------------------------------------------------------------------------------------------------------------------------------------|---------------------------------------------------------------------------------------------------------------------------------------------------------------------------------------------------------------------------------------------------------------------------------------|
|                                                                                                                  | Lenalidomide                                                                                                                                                                                                                                                                   | Carfilzomib                                                                                                                                                                                                                                                                    |
| Blood clot in the lungs, fluid in the lungs, bleeding in the lungs                                        | NA                                                                                                                                                                                                                                                                                    | ≥ Grade 3: carfilzomib attribution, hold drug until resolved to ≤ Grade 1. Resume at one level dose reduction                                                                                                                                                                         |
| Gastrointestinal Perforation                                                                              | NA                                                                                                                                                                                                                                                                                    | ≥ Grade 3: carfilzomib attribution, hold drug until resolved to Grade 1. Resume at one level dose reduction                                                                                                                                                                           |
| Hepatic Toxicities (≥ Grade 3 elevation of AST or ALT, Bilirubin, or other ≥ Grade 3 liver abnormalities) | Hold drug until resolved to ≤ Grade 1 or baseline. Resume at the same dose or reduced dose as appropriate. If tolerated, the reduced dose may be escalated to the previous dose at the discretion of the physician. Frequent monitoring of liver function should then be implemented. | Hold drug until resolved to ≤ Grade 1 or baseline. Resume at the same dose or reduced dose as appropriate. If tolerated, the reduced dose may be escalated to the previous dose at the discretion of the physician. Frequent monitoring of liver function should then be implemented. |
| Other non-hematologic toxicity assessed as lenalidomide-related ≥ Grade 3                                 | Hold lenalidomide dose. Follow at least weekly.

If the toxicity ≤ Grade 1 before Day 21 of the current cycle, restart at 1 dose decrement and continue until Day 21 of the current cycle                                                                                       | Full dose                                                                                                                                                                                                                                                                             |
| Other non-hematologic toxicity assessed as carfilzomib-related ≥ Grade 3                                  | Full dose                                                                                                                                                                                                                                                                             | Hold carfilzomib dose until toxicity resolves to ≤ Grade 1 or baseline. Restart at 1 dose decrement                                                                                                                                                                                   |
| Other non-hematologic toxicity assessed as drug-related ≥ Grade 3                                         | Hold treatment and restart at 1 dose decrement when toxicity has resolved to ≤ Grade 1 or baseline                                                                                                                                                                                    | Hold treatment and restart at 1 dose decrement when toxicity has resolved to ≤ Grade 1 or baseline                                                                                                                                                                                    |

#### 6.5.1.4 Toxicity Management for Dexamethasone

Please refer to **Table 6-9** below for dose modifications for Dexamethasone regarding toxicities related to Dexamethasone.

**Table 6-9 Dose Modification Guidelines for Toxicity Related to Dexamethasone**

| BODY SYSTEM      | SYMPTOM                                                                                                        | RECOMMENDED ACTION                                                                                                                                                                                                                          |
|-------------------------|-----------------------------------------------------------------------------------------------------------------------|----------------------------------------------------------------------------------------------------------------------------------------------------------------------------------------------------------------------------------------------------|
| Gastrointestinal | Dyspepsia, gastric or duodenal ulcer, gastritis
Grade 1-2 (requiring medical management)                           | Treat with H2 blockers, sucralfate, or omeprazole. If symptoms persist despite above measures, decrease dexamethasone dose by 1 dose level.                                                                                                        |
| Gastrointestinal | ≥ Grade 3 (requiring hospitalization or surgery)                                                                      | Hold dexamethasone until symptoms adequately controlled. Restart at 1 dose decrement along with concurrent therapy with H2 blockers, sucralfate, or omeprazole. If symptoms persist despite above measures, discontinue dexamethasone permanently. |
| Gastrointestinal | Acute pancreatitis                                                                                                    | Discontinue dexamethasone permanently.                                                                                                                                                                                                             |
| Cardiovascular   | Edema ≥ Grade 3 (limiting function and unresponsive to therapy or anasarca)                                           | Diuretics as needed, and restart dexamethasone at 1 dose decrement; if edema persists despite above measures, decrease dose another level. Discontinue dexamethasone permanently if symptoms persist despite second reduction.                     |
| Neurology        | Confusion or mood alteration
> Grade 2 (interfering with function +/- interfering with activities of daily living) | Hold dexamethasone until symptoms resolve. Restart at 1 dose decrement. If symptoms persist despite above measures, discontinue dexamethasone permanently.                                                                                         |
| Musculoskeletal  | Muscle weakness > Grade 2 (symptomatic and interfering with function +/- interfering with activities of daily living) | Decrease dexamethasone by 1 dose level. If weakness persists, decrease dose by 1 more dose level. Discontinue dexamethasone permanently if symptoms persist.                                                                                       |
| Metabolic        | Hyperglycemia ≥ Grade 3                                                                                               | Treatment with insulin or PO hypoglycemic agents as needed. If uncontrolled despite above measures, decrease dose by 1 dose level until levels are satisfactory.                                                                                   |

### 6.5.2 Response Evaluation

The first response assessment should be completed at screening (for stratification purposes) and the M-spike value will be compared to pre-induction (prior to transplant) M-spike to determine response. If the pre-induction value is not available, the closest value to initiation of induction will be used as baseline for

all assessments, including response at screening and every cycle while on protocol treatment thereafter. If M-spike is not available, the respective pre-treatment immunoglobulin level and for light-chain-disease-only subjects, involved free light chain level or 24-hr total protein level, will be used to assess response. If at any time throughout the treatment a complete response or better is suspected, a complete disease assessment should be performed to confirm response according to IMWG criteria:

|                                         |                                                                                                                                                                                                                                                                                                                                                                                                                                                                                                                                           |
|-----------------------------------------|-------------------------------------------------------------------------------------------------------------------------------------------------------------------------------------------------------------------------------------------------------------------------------------------------------------------------------------------------------------------------------------------------------------------------------------------------------------------------------------------------------------------------------------------|
| Myeloma Disease Assessment – laboratory | M-protein determination: 
 
• Serum protein electrophoresis and immunofixation
 
• Urine protein electrophoresis and immunofixation
 
• Serum free light chains and Hevylite test
 
• Serum quantitative immunoglobulins
 
                                                                                                                                                                                                                                              |
| Bone Marrow Biopsy                      | Quantify percent myeloma cell involvement, and obtain bone marrow aspirate for conventional cytogenetics and fluorescent in situ hybridization. For subjects who give consent for correlative samples, an additional aspirate sample should be collected at screening, at time of complete response and/or progressive disease (if applicable), at the end of Cycles 8, 24, and then yearly for as long as no PD up to 2 years. If a CR is suspected after Cycle 8, a bone marrow biopsy will be completed at Cycle 12 to confirm. |
| Radiographic Imaging                    | As per standard of care                                                                                                                                                                                                                                                                                                                                                                                                                                                                                                                   |

Progressive disease requires 2 consecutive assessments made at any time before classification of relapse or progression and/or institution of new therapy when clinically possible.

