##### **4.1.2.2 Treatment Phase**

Treatment will be continued until progression of disease according to IMWG criteria, unacceptable toxicities occur in individual subjects or consent is withdrawn. Cycles 1 through 4 are considered D-KRd induction cycles, Cycle 5-8 D-KRd consolidation, and Cycles 9-24 D-KRd maintenance cycles. After Cycle 4, subjects who are deemed candidates for ASCT will proceed to stem cell harvest as per institutional guidelines. However, the study design recommends a “delayed” transplant for ASCT candidates, as in subject having completed frontline KRd study without or with delayed transplant. This means that patients who are transplant candidates enrolled in this study will not proceed to ASCT; rather, they will have cells frozen down for a potential future transplant at progression or unacceptable toxicity after Cycle 4. After completion of stem cell harvest, patients will resume protocol treatment.

In the event that a subject’s risk status is unknown at the time of study entry, the subject will be required to re-consent to continue participation in this study if it is later determined that the subject has high-risk disease status and therefore may benefit from ASCT.

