## 5 Patient Selection

### 5.1 Inclusion Criteria

Subjects must meet all of the following inclusion criteria to be eligible to enroll in this study. No enrollment waivers will be granted.

1. Newly diagnosed, previously untreated myeloma requiring systemic chemotherapy
  - Prior treatment of hypercalcemia or spinal cord compression or active and/or aggressively progressing myeloma with corticosteroids or lenalidomide or bortezomib-based regimens does not disqualify the patient (the treatment dose should not exceed the equivalent of 160 mg of dexamethasone in a 4-week period or not more than 1 cycle of PI/IMiD-based therapy).
2. Both transplant and non-transplant candidates are eligible
3. Diagnosis of symptomatic multiple myeloma as per current IMWG uniform criteria prior to initial treatment
4. Monoclonal plasma cells in the BM  $\geq 10\%$  or presence of a biopsy-proven plasmacytoma
5. Measurable disease, prior to initial treatment including any emergent treatment of myeloma. Measurable disease will be indicated by one or more of the following:
  - Serum M-protein  $\geq 1$  g/dL
  - Urine M-protein  $\geq 200$  mg/24 hours
  - If serum protein electrophoresis is felt to be unreliable for routine M-protein measurement, then quantitative immunoglobulin levels are acceptable

- Serum Freelite measurable disease as per current IMWG criteria
6. Bone marrow specimen will be required at study entry; available DNA sample from pre-induction BM will be used for calibration step for MRD evaluation by gene sequencing
  7. Males and females  $\geq 18$  years of age
  8. ECOG performance status of 0-1
  9. Adequate hepatic function, with bilirubin  $\leq 1.5 \times \text{ULN}$  and aspartate aminotransferase (AST) and alanine aminotransferase (ALT)  $\leq 3 \times \text{ULN}$
  10. ANC  $\geq 1.0 \times 10^9/\text{L}$ , hemoglobin  $\geq 8 \text{ g/dL}$ , platelet count  $\geq 75 \times 10^9/\text{L}$
  11. Calculated creatinine clearance (by Cockcroft-Gault)  $\geq 50 \text{ mL/min}$  or serum creatinine below  $2 \text{ g/dL}$
  12. FCBP must have 2 negative pregnancy tests (sensitivity of at least  $50 \text{ mIU/mL}$ ) prior to initiating lenalidomide. The first pregnancy test must be performed within 10-14 days before and the second pregnancy test must be performed within 24 hours before lenalidomide is prescribed for Cycle 1 (prescriptions must be filled within 7 days).

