### **7 SAMPLES FOR MRD EVALUATION AND CORRELATIVE SAMPLES**

Bone marrow samples for MRD evaluation are required and as per the standard of care and will be collected prior to initiation of any MM treatment (pre-induction), screening, at the completion of 8 cycles

of D-KRD, at 24 months and then yearly, or at the time of progression/relapse for up to 2 years. If a CR is suspected after Cycle 8, a bone marrow biopsy and MRD testing will be completed at Cycle 12.

Additionally, provided that the patient consents, correlative samples will be collected and banked for further research studies.

| MRD sample                                                                                | Correlative Sample | Time Points                                                                                                                                                                                                                                                                                                              |
|--------------------------------------------------------------------------------------------------|---------------------------|---------------------------------------------------------------------------------------------------------------------------------------------------------------------------------------------------------------------------------------------------------------------------------------------------------------------------------|
| Bone Marrow Aspirate (MRD samples) or FFPE/BMA slides (ID/calibration sample from pre-treatment) | Bone Marrow Aspirate      | Pre-treatment (calibration sample for MRD only), screening, at end of 8, and 24 cycles, or EOT, yearly after EOT up to 2 years, and at the time of complete response (if applicable: If a CR is suspected after cycle 8, a bone marrow biopsy and MRD testing will be completed at cycle 12 to confirm.)
Progression/Relapse |
|                                                                                                  | Peripheral Blood          | Screening, at end of 8 and 24 cycles or EOT, yearly after EOT up to 2 years, and at the time of complete response (if applicable; If a CR is suspected after cycle 8, a bone marrow biopsy and MRD testing will be completed at cycle 12 to confirm)
Progression/Relapse*                                                    |

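### Section 6.5.2 scores a response at screening under a rule that does not fit this trial, so a pre-treated patient can be recorded in PR before the first D-KRd dose; only secondary measures are exposed

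*Protocol*

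**What the plan says.** Protocol Section 6.5.2 opens: "The first response assessment should be completed at screening (for stratification purposes"). It continues that "the M-spike value will be compared to pre-induction (prior to transplant) M-spike to determine response". Where that value is missing, the one nearest the start of induction takes its place, and the resulting reference covers "all assessments, including response at screening and every cycle while on protocol treatment thereafter". One baseline rule thus governs both the screening score and every later score.

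The surrounding sections use the key word in two ways. Section 7 lists MRD marrow samples as "collected prior to initiation of any MM treatment (pre-induction), screening", so pre-induction there means before any myeloma treatment and is a time point separate from screening. Section 4.1.2.2 states that "Cycles 1 through 4 are considered D-KRd induction cycles", so induction there is study treatment.

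Inclusion criterion 1 (Section 5.1) allows limited prior corticosteroid, lenalidomide- or bortezomib-based treatment: a capped dexamethasone-equivalent dose "or not more than 1 cycle of PI/IMiD-based therapy". Inclusion criterion 5 requires "Measurable disease, prior to initial treatment including any emergent treatment of myeloma".

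Two other places set a later start. Section 4.1 has treatment response assessed from Cycle 2 Day 1. Appendix 8 footnote 17 says the Cycle 1 Day 15 disease assessments look only for early onset and do not establish response definitively.

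**The concern.** The rule appears written for another design. All patients here receive one regimen and Section 10 names no stratified analysis, so a screening response has nothing to stratify. Transplant is deferred (Section 4.1.2.2), so no transplant precedes screening.

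The rule also has an effect. PR, and the M-protein-reduction route to VGPR, are falls from baseline (Appendix 4). If the baseline precedes emergency therapy and the first score is taken at screening, that therapy alone can produce a recorded response. Nothing in the protocol excludes a response already present at screening. In a single-arm trial, response rates and duration of response are read as results of D-KRd, so the record should not allow a response to begin before D-KRd does.

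**Working it through.** The plan states no figure to reproduce. The check traces the rule and then sizes it under assumptions.

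**1. Which reading of pre-induction gives the rule content?** If it means before D-KRd (Section 4.1.2.2), the screening M-spike is compared with itself or a near-simultaneous value, and a screening response means nothing. If it means before any myeloma treatment (Section 7), the comparison has content. The second reading is the more natural one, but the protocol does not settle it.

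**2. A hypothetical patient.** M-spike 4.0 g/dL before emergency therapy; 1.8 g/dL at screening after one PI/IMiD cycle; 1.8 g/dL on D-KRd. Assume the urine and plasmacytoma criteria for PR are met.
- At screening, against the pre-treatment value: (4.0 − 1.8)/4.0 = 55%, which passes the 50% PR threshold before dose 1.
- On D-KRd, same baseline: still 55%, so PR.
- On D-KRd, against the last value before Cycle 1 Day 1: (1.8 − 1.8)/1.8 = 0%, so not PR.

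The flat on-treatment value only shows what the rule does; it is not a prediction.

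**3. Mixed baselines.** Let the on-treatment value be 1.2 g/dL. Against 4.0 the fall is (4.0 − 1.2)/4.0 = 70%, PR. Against 1.8, which the fallback could supply if induction means D-KRd, it is (1.8 − 1.2)/1.8 = 33%, not PR. Two identical patients could be scored differently depending on which value is on file. Inclusion criterion 5 should make a missing pre-treatment value uncommon.

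**4. Which endpoints use the baseline?**

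| Measure | Uses the M-spike baseline? |
|---|---|
| PR; VGPR by M-protein reduction; overall response rate | Yes |
| Duration of response | Only if counted from the first recorded response |
| CR, sCR | No: negative immunofixation and marrow criteria |
| MRD negativity by NGS | No |

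The primary test uses sCR and/or MRD negativity, so this rule does not touch it.

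**5. Possible size.** Let *f* be the share pre-treated and *q* the share of those already at the response level at screening. The documents give neither. I assume *f* = 5% to 50% and *q* = 20% to 80%, deliberately wide.
- Patients already at PR or better before dose 1 = 45 × *f* × *q*: from 45 × 0.05 × 0.20 = 0.45 to 45 × 0.50 × 0.80 = 18.
- Rise in a best-response rate = *f* × *q* × (1 − true rate), taking the true rate to be the same in pre-treated patients.
 - Overall response, true rate 98% (historical KRd, Section 1.7): 0.01 × 0.02 = 0.02 points to 0.40 × 0.02 = 0.8 points.
 - VGPR or better, true rate 87% (same source), with *q* read as the share at VGPR or better at screening: 0.01 × 0.13 = 0.13 points to 0.40 × 0.13 = 5.2 points.

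**6. Duration of response.** Screening opens on Day −21. If duration runs from the first recorded response, up to 21 days before any D-KRd could be counted in the affected patients.

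**The case against.** The best defence is that a pre-treatment reference is deliberate and coherent. Inclusion criterion 5 and exclusion criterion 2 both assess measurability before initial treatment, and where no M-spike exists Section 6.5.2 substitutes the pre-treatment immunoglobulin level. Having admitted patients on their pre-emergency disease, scoring from that value makes sense, and prior therapy is limited. Section 6.5.2 also gives the screening score its own purpose, stratification, and Section 4.1 and footnote 17 suggest that nobody intends a pre-dose value to count as a D-KRd response. This stands to a large extent: the pre-treatment baseline is not the error. What it leaves is a screening response with no function here, in conflict with two other places, under a term with two meanings.

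A reader might infer more than the text supports:
- **That time to response would become negative.** Section 10.2.2 times only sCR and MRD negativity from first treatment, and neither uses this baseline. Time to PR is not a listed endpoint.
- **That duration of response does start before Cycle 1 Day 1.** The protocol does not define its start; a statistical analysis plan may.
- **That a known share of patients would be responders owing nothing to D-KRd.** Neither the pre-treated share nor the response to prior therapy is given.
- **That a patient entering in PR should count only on reaching a deeper category.** Nothing in the documents requires this, and it would make a non-responder of someone who holds PR throughout.

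**Conclusion.** The point holds as a defect of rule and wording with limited reach. As written, Section 6.5.2 can record a PR before the first D-KRd dose in a pre-treated patient, if Section 7's sense of pre-induction applies and the urine and plasmacytoma criteria are met. This contradicts Section 4.1 and footnote 17 of Appendix 8.

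The exposure is confined to early PR and VGPR rates and, conditionally, the start of duration of response. The true size cannot be derived from the protocol. Best overall response would barely move if it is near 98%; VGPR has more room, though the top of its range needs implausibly heavy pre-treatment and response. The primary conclusion does not depend on this point. It is minor, but worth correcting because the correction is nearly free.

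**What to change.** In Section 6.5.2:
- Delete the response assessment at screening and the references to stratification and transplant. Keep the screening laboratory values.
- Define one baseline for all patients and use one term for it. The value before any myeloma treatment is consistent with inclusion criterion 5. State the fallback without the word induction.
- Reconcile the section with Section 4.1 so that response, and duration of response, can start only at an assessment after Cycle 1 Day 1.

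In reporting, flag pre-treated patients when giving PR and VGPR rates. Add a sensitivity analysis against the last value before Cycle 1 Day 1 where disease is still measurable. This is needed because a pre-treatment baseline still mixes the effects of prior therapy and D-KRd after the screening score is removed.

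The cost is a wording amendment. Prior therapy is already collected at screening (Section 6.1.1), so no new data are needed. Duration of response and early response rates may look marginally less favourable; the primary analysis does not change.
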